### Feasibility

In addition to the outcomes, the study will assess feasibility by examining (1) time to recruit 400 couples to the intervention and (2) rate of recruitment per 100 men expressing interest in participation. Acceptability of the intervention will be determined by analysis of data from the satisfaction survey on the intervention’s acceptability to couples. In addition, the percentages of male couples who do not complete the home-testing profile and the percentage of those not returning test results via the study website will be analyzed.

### Cost Analysis

To examine the cost of the proposed intervention, cost data are collected by input type and by activity, using an activity-based costing matrix. Input types include study personnel salaries and benefits, supplies, equipment, HIV testing kits, and training materials. Activities include training (ie, counselors and crisis counseling), recruitment of participants, VSee video-based chat, follow-up, and linkage to care. For the experimental arm, counselors record the time spent per session of the counselor because these are the only additional (ie, incremental) costs incurred relative to the control arm.

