#### Intervention

The proposed intervention is a combination of home-based HIV testing and CHTC offered remotely via VSee video chat. In the control arm, couples receive one or two home-based HIV testing kits based on the couple’s serostatus; the partner living with HIV in a serodiscordant couple does not repeat HIV testing. These kits sent to couples in the control arm contain one or two HIV testing kits as well as instructions on how to use the kits and how to report their test results in the study portal. In the experimental arm, couples receive one or two home-based HIV testing kits and complete the testing while undergoing a remote, VSee video-based CHTC session. Individual participants testing positive in either the experimental or the control condition are linked to their preference of local HIV care-specific resources within 48 hours. They will receive another HIV test at their preferred local HIV care-specific resource to validate the preliminary positive test result. These participants will receive follow-up from the CHTC counselor at 1-week, 1-month, and 3-month postresult of HIV-positive status to assess their engagement in care.

For couples randomized to the experimental arm, an email informs them that they have the opportunity to receive one or two home-based HIV testing kits and to take part in a video-based counseling session. The email provides details on the expected content of a CHTC session, the expectation that both partners will need to conduct their individual HIV tests and receive their results together in the presence of a remote counselor, as well as further logistical information (ie, length of the counseling session). From this email, couples are instructed to log on to the study website to order their HIV testing kits, with the same options as the control arm. Figure 1 shows the log-in page that users see when logging on to the Project Nexus website. For those randomized to receive HIV home testing with CHTC, they are asked to select a CHTC appointment time via an electronic calendar, which is shown in Figure 2. To allow intent-to-treat analysis, couples who do not complete the CHTC session and do not schedule an appointment, as well as couples in the control arm who do not report their HIV test results, are able to move on to take the 3-month and 6-month surveys.

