The CHTC session is conducted via video chat using VSee. Figure 3 is an example of the VSee interface that participants see when waiting for their prescheduled counseling session to begin. The session is conducted by a counselor who is trained in CHTC and will last approximately 30-45 minutes. Pretest counseling focuses on the couple’s relationship, their perceived HIV risk factors, and focuses on their sexual agreement. Both partners individually conduct their own HIV test and read their individual results together, as instructed by the counselor. Participants are asked to show the counselor their test result; the counselor then confirms the test result for accuracy of interpretation. Figure 4 is the interface the participant sees when entering their HIV testing result to the Nexus website. Posttest counseling focuses on dyadic prevention messages and revisits the couple’s HIV risk concerns and sexual agreements in light of their test results. The counselor records the couple’s HIV test results in the couple’s study file. The counselor is trained to keep focus on the couple in the event that an HIV-positive result is given during a CHTC session. While a focus on the immediate needs of the HIV-positive partner is required, the discussion remains focused on how the couple can work together to keep the positive partner healthy and to keep the risk of HIV within, and not outside of, the relationship with other partners, while also meeting the needs of both partners within the male couple. If both couples are seroconcordant negative, the counselor discusses strategies that will minimize the risk of HIV transmission within and/or outside the relationship. The prevention-counseling element of the CHTC session focuses on talking the couple through prevention options and asking them to consider which prevention options may work best based on their relationship needs, context, and unique risk profile.

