## Discussion

Online CHTC via video chat provides an opportunity to expand CHTC to male couples who (1) live outside metro areas, (2) live in rural areas without access to testing services or LGBTQ resources, or (3) feel that current clinic-based testing is not for them (eg, due to fears of discrimination associated with HIV and sexuality). Although home-based HIV testing is now a reality, many still question the lack of counseling available to those who are undergoing testing in the individual household. A video-chat-based CHTC session potentially provides an inexpensive way to remedy this problem and provides an opportunity for those receiving an HIV-positive result to receive assistance in linkage to care. The proposed activities not only have the potential to expand CHTC to male couples who currently do not have access, but may provide opportunities to improve the utility of home-based testing for couples by providing them a forum to discuss prevention planning with a counselor. It is true that some individuals use home-based HIV testing because they do not want counseling and the proposed intervention would probably not be adopted by those people. However, for couples who desire and/or need counseling and do not have access due to physical or sociocultural barriers, a low-cost, video-based counseling session provides the opportunity to reach them, create HIV prevention planning, and locate linkage to care in a safe and comfortable environment.

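### Counselor session time is declared the only incremental cost, which contradicts the costing matrix in the same paragraph and the descriptions of the two arms

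*Protocol article*

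**What the plan says.** The Cost Analysis section describes activity-based costing by input type and by activity. On inputs: "Input types include study personnel salaries and benefits, supplies, equipment, HIV testing kits, and training materials". On activities: "Activities include training (ie, counselors and crisis counseling), recruitment of participants, VSee video-based chat, follow-up, and linkage to care". It then gives the rule for the comparison between arms: "For the experimental arm, counselors record the time spent per session of the counselor", and the reason is "because these are the only additional (ie, incremental) costs incurred relative to the control arm".

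The Intervention section describes what each arm receives. Control-arm packages "contain one or two HIV testing kits as well as instructions on how to use the kits" and how to report the results. Experimental couples also receive kits, but they "complete the testing while undergoing a remote, VSee video-based CHTC session", at a time they choose on an electronic calendar. On delivery: "The session is conducted by a counselor who is trained in CHTC and will last approximately 30-45 minutes". The same section assigns the CHTC counselor to follow up participants who test positive in either arm, at 1 week, 1 month and 3 months.

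**The concern.** The reason given for logging session time is a categorical statement about every cost that separates the two arms. It leaves out the video platform and the training needed to run the session, although the matrix a few lines above lists both as costed items. If the analyst follows it, the incremental cost is priced from session minutes alone.

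What is at stake is the affordability message. The Discussion says: "A video-chat-based CHTC session potentially provides an inexpensive way to remedy this problem". A program that already distributes home test kits and is thinking of adding the session would want to know what the addition costs. That includes training counselors and running the platform, not just counselor minutes.

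**Working it through.** The article states no cost figure, so there is nothing to reproduce. The check compares the rule with the article's own description of the arms, item by item.

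| Item in the matrix | Control arm | Experimental arm | Incremental? |
|---|---|---|---|
| HIV testing kits | yes | yes | no |
| Counselor session time | no | yes | yes, and recorded as such |
| VSee video chat and related equipment | no video session | yes | yes, but excluded by the rule |
| Counselor training and materials for the CHTC session | not needed for solo testing | needed | yes for that part, but excluded by the rule |
| Crisis-counseling training | may be used | may be used | partly at most; needs allocation |
| Counselor follow-up and linkage after a positive test | yes | yes | shared activity; needs allocation |

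Two rows carry costs that arise because of the experimental session and are not session time. Leaving out a positive cost specific to the experimental arm can only lower the incremental figure, so the direction of the bias follows from the text.

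**Size, as an illustration only.** Work in counselor hours, so that no wage is needed. Let S be total session hours in the experimental arm, T the training effort in counselor-hour equivalents, and f the fraction of T attributable to the video session. The share of true incremental cost omitted by the rule is fT / (S + fT).

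Inputs from the article:
- Session length is 30–45 minutes, that is 0.5–0.75 h (Intervention).
- The target is 100 couples of each serostatus type per arm, that is 200 experimental couples (Sample Size).
- The same section also projects 425 couples randomized per arm, used here as an alternative.

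Assumptions not in the article: T = 20–100 hours, f = 1 or 0.5, platform and equipment cost zero, and every couple completes one session.

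Session hours:
- 200 couples: S = 200 × 0.5 to 200 × 0.75 = 100 to 150 h.
- 425 couples: S = 425 × 0.5 to 425 × 0.75 = 212.5 to 318.75 h.

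Omitted share, lowest (small T, large S) to highest (large T, small S):
- 200 couples, f = 1: 20/(150 + 20) = 12% to 100/(100 + 100) = 50%.
- 200 couples, f = 0.5: 10/(150 + 10) = 6% to 50/(100 + 50) = 33%.
- 425 couples, f = 1: 20/(318.75 + 20) = 6% to 100/(212.5 + 100) = 32%.
- 425 couples, f = 0.5: 10/(318.75 + 10) = 3% to 50/(212.5 + 50) = 19%.

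A positive platform or equipment cost would raise each figure. So would incomplete uptake, because training is then spread over fewer session hours; the Results section reports 85 of 111 intervention couples (76.6%) with a completed session. The width of these ranges shows how little the article fixes.

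**The case against.** The strongest reply is that the sentence only explains a data-collection step, namely why counselors keep a time log. The section says its purpose is to examine the cost of the intervention, and it defines no incremental-cost estimator or cost-effectiveness ratio. Training, equipment and VSee are in the matrix, and nothing says they will be dropped from the reported cost. An article may also leave allocation rules to a fuller costing plan.

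Much of this stands. A reader might infer that the cost of the intervention as a whole will be understated; the documents do not support that, because the matrix covers the omitted items. A reader might also infer that control couples make no use of the counselor, so that all training belongs to the experimental arm. The Intervention section shows otherwise, since the CHTC counselor follows up positive results in both arms. Staff costs for scheduling or missed appointments are possible, but the article neither describes nor prices them. The Discussion's remark on cost is hedged and does not draw on this costing.

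The categorical statement itself remains. It is not a detail left to another document: the article asserts that nothing else is incremental, and its own description of the arms shows that this is not so. Partial sharing of training calls for allocation; it does not justify counting none of it.

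**Conclusion.** The point holds in a limited form. The claim that session time is the only incremental cost contradicts both the matrix beside it and the arm descriptions. If incremental cost is computed on that claim, it is biased downward. The direction rests only on the VSee session, and the training to deliver it, having some cost. The size cannot be determined from the documents; the 3% to 50% range above rests on assumed training hours and an assumed attributable fraction, and should not be cited as an estimate.

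A reader might take cost to be one of the trial's aims and rate the issue accordingly. The Objective and the outcome sections do not include it; it is a planned descriptive analysis. No efficacy or safety inference depends on it. The statement should be corrected, but it is no threat to the trial's main conclusions.

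**What to change.** Delete the claim that session time is the only additional cost, and choose one of two courses.

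1. Define incremental cost as experimental-arm cost minus control-arm cost across all activities in the matrix, including VSee and session-specific training. State how training and counselor follow-up that serve both arms are divided between them.
2. Keep the present quantity, but call it the marginal counselor time cost per session and report training and platform costs alongside it.

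Either course is mainly a change of wording and draws on items the matrix already covers. The price is a little allocation work and, under the first course, a somewhat less favourable incremental cost.

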### Incentives

Individual participants each receive US $50 for completing each of the main three surveys: the baseline, the 3-month follow-up, and the 6-month follow-up. If all surveys are completed by both members of the male couple, the total incentive amount is US $300 per couple (US $150 per individual participant).

### Sample Size

The goal is to enroll and maintain a sample of 400 male couples: 200 serodiscordant and 200 seroconcordant couples, 100 of each couple per arm (experimental vs control). To achieve this, the intervention aims to screen approximately 1000 male couples—500 serodiscordant and 500 seroconcordant male couples—and will exclude those with a recent (<12 months) history of IPV. Assuming 15% of male couples have a recent history of IPV, this will produce approximately 850 couples for randomization, 425 per arm. Allowing for 20% loss to follow-up and additional 20% relationship dissolution, this will produce a sample of 400 male couples who are expected to complete the prospective RCT. The sample size is calculated based on the detection of significant changes in each of the main outcomes (ie, changes in sexual risk-taking, such as CAI), formation and adherence to explicit sexual agreements, and relationship functioning for the management of HIV risk. As an example, we will assume that about 25% of male couples change agreement status after couples counseling and we will use a two-sample test of binomial proportions with type I error rate at 5%. Using these assumptions, it is determined that 52%, 67%, and 85% statistical power is necessary to detect a difference of 10%, 12%, and 15%, respectively, in a change-of-agreement status between the two arms within seroconcordant or serodiscordant groups (ie, comparing 150 male couples per arm). In other words, under the same conditions, the probability is .52, .67, and .85 that the lower bound of the confidence interval for the proportion change in agreement status in the intervention arm is at least 3%, 5%, and 8% different than the proportion in the control arm, respectively, when the alternative hypothesis is true. If data is pooled across seroconcordant and serodiscordant couples, assuming that combining data makes sense in terms of the magnitude and direction of the intervention effect, then 81%, 92%, and 99% statistical power is necessary to observe differences of 10%, 12%, and 15%, respectively (ie, comparing 300 male couples per arm). In this case, at least 80% statistical power will be necessary to detect as little as a 5% difference between the lower bound of the confidence interval for the proportion in the intervention versus the control arm. Based on discussions with participant advocates and partnered community-based organizations, it is projected that any difference exceeding 5% would be scientifically meaningful and would have public health impact. The analysis also considers differences in linkage to HIV care among HIV-positive individuals in each arm, but it is not powered to detect significant differences, given the small number of incident positive cases.

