**Methods:**

The research implements a prospective RCT of 400 online-recruited male couples: 200 self-reported concordant-negative couples and 200 self-reported discordant couples. Couples in the control arm will receive one or two home-based HIV self-testing kits and will be asked to report their results via the study’s website. Couples in the experimental arm will receive one or two home-based HIV self-testing kits and will conduct these tests together under the facilitation of a remotely located counselor during a prescheduled VSee-based video CHTC session. Study assessments are taken at baseline, as well as at 3- and 6-month follow-up sessions.

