
## Methods

### Description of Trial and Intervention

#### Design

The research activities involved a blind prospective RCT of approximately 400 online-recruited male couples—200 self-reported concordant-negative couples and 200 self-reported discordant couples. Couples in the control arm will receive one or two home-based HIV self-testing kits and will be asked to report their results via the study’s website. One kit will be provided for each person who reports to have previously tested HIV-negative or unknown status; partners in serodiscordant couples who report living with HIV will not be retested. Couples in the experimental arm will receive one or two home-based HIV self-testing kits and will conduct these tests together under the facilitation of a remotely located counselor during a prescheduled VSee-based video CHTC session.

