#### Randomization

Upon individual completion of the baseline survey by both partners, couples are randomized to either the home-based HIV testing arm or video-based CHTC with home-based HIV testing arm using a stratified 1:1 treatment allocation. The strata are based on two levels of serostatus: seroconcordant negative and serodiscordant. The treatment assignments are generated with the use of a pseudo-random number generator with permutated blocks that are used to ensure balance within stratum between the numbers of couples assigned to each treatment. The randomization process generates one of two emails to both study participants for the enrolled male couple, indicating whether they will be receiving home-based HIV testing or video-based CHTC with home-based HIV testing.

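### The power figures are computed for 150 and 300 couples per arm, but the planned 400 couples give 100 and 200 per arm, where the same method gives lower power

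*Protocol article*

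**What the plan says.** The Sample Size section sets a goal of "400 male couples: 200 serodiscordant and 200 seroconcordant couples, 100 of each couple per arm (experimental vs control"). The abstract agrees ("200 self-reported concordant-negative couples and 200 self-reported discordant couples"), and the Design section describes a "blind prospective RCT of approximately 400 online-recruited male couples". Couples are allocated "using a stratified 1:1 treatment allocation", with couple serostatus as the stratum. The comparison is therefore 100 against 100 within a stratum and 200 against 200 when strata are pooled.

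The same Sample Size paragraph takes about 25% of couples changing agreement status after couples counseling, a two-sample binomial test and a 5% type I error rate. It then gives two sets of power for differences of 10, 12 and 15 percentage points:

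- 52%, 67% and 85% for a difference "in a change-of-agreement status between the two arms within seroconcordant or serodiscordant groups (ie, comparing 150 male couples per arm");
- 81%, 92% and 99% with strata pooled ("ie, comparing 300 male couples per arm").

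It also describes about 850 couples for randomization (425 per arm), followed by 20% loss to follow-up and a further 20% relationship dissolution, and says this leaves 400 couples completing.

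**The concern.** Two strata of 150 per arm, or 300 per arm pooled, make 600 analysed couples. The article plans 400 and nowhere explains the other 200. If the percentages were calculated at 150 and 300, they describe a larger trial than the one planned.

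This is the only power calculation the article gives for any outcome. The pooled 10-point difference is the smallest one said to have about 80% power, and the section calls any difference above 5 points meaningful. Someone relying on the printed power could read a null result as stronger evidence against a 10- to 15-point effect than the trial can supply.

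**Working it through.** **Inputs (Sample Size section).** Rate 25%, alpha 5%, differences d = 0.10, 0.12 and 0.15. Couples per arm: 150 and 300 in the power statement, 100 and 200 in the planned sample. Two inputs are not stated and are assumed here: a two-sided test, and 25% as the mean of the two arms (p1 = 0.25 − d/2, p2 = 0.25 + d/2). They are chosen because they reproduce the printed figures.

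**Formula.** Power = Φ[(d − 1.96·SE0)/SE1], with SE0 = √(2·p̄(1−p̄)/n), SE1 = √((p1(1−p1) + p2(1−p2))/n) and p̄ = (p1 + p2)/2.

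**Step 1: reproduce the plan's figures.** For d = 0.10 and n = 150, p1 = 0.20 and p2 = 0.30. SE0 = √(2×0.25×0.75/150) = 0.0500 and SE1 = √((0.16+0.21)/150) = 0.0497. Then (0.10 − 1.96×0.0500)/0.0497 = 0.04, and Φ(0.04) = 51.6%.

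| n per arm | 10 points | 12 points | 15 points | Stated |
|---|---|---|---|---|
| 150 | 51.6% | 67.2% | 85.5% | 52/67/85% |
| 300 | 80.9% | 92.6% | 99.0% | 81/92/99% |

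All six agree within one point. Solving back for n from each stated power gives 149 to 152 and 293 to 302 per arm. The percentages therefore belong to 150 and 300, and changing only those two numbers in the text would leave the percentages wrong.

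**Step 2: same method at the planned size.** For d = 0.10 and n = 100, SE0 = 0.0612 and SE1 = 0.0608. Then (0.10 − 1.96×0.0612)/0.0608 = −0.33, and Φ(−0.33) = 37.1%.

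| n per arm | 10 points | 12 points | 15 points | Fall from stated |
|---|---|---|---|---|
| 100 (within stratum) | 37.1% | 50.0% | 69.0% | about 15, 17, 16 points |
| 200 (pooled) | 63.8% | 79.4% | 93.7% | about 17, 13, 5 points |

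Difference detectable with 80% power: 17.1 points at n = 100 (14.0 at 150), and 12.1 points at n = 200 (9.9 at 300).

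**Step 3: other readings of the 25%, two-sided.**

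| Reading | 100 per arm | 200 per arm |
|---|---|---|
| 25% is the control rate (25% vs 35/37/40%) | 34/45/62% | 59/74/90% |
| 25% is the higher rate (25% vs 15/13/10%) | 42/58/80% | 71/87/98% |

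Neither reading reproduces the stated figures at 150 and 300: the first gives 47/61/80% and 76/89/98%, the second 58/76/93% and 87/97/99.8%. At 100 and 200 per arm, every value under both readings is below the stated one.

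**Step 4: does the attrition chain explain 150 and 300?** 850 × 0.8 × 0.8 = 544 couples, or 136 per arm per stratum and 272 pooled. 850 × (1 − 0.2 − 0.2) = 510, or about 127 and 255. Neither gives 600, and neither gives the stated 400. With 544 completers the centred, two-sided powers are 48/63/82% and 77/90/98%, between one and four points below those stated.

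**The case against.** The inconsistency itself is hard to dispute, but its size can be.

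- **Sidedness and the 25% are not stated.** The text ties the 25% to couples who have been counseled, so taking it as the intervention-arm rate is natural. If that is also the higher rate, the shortfall is smaller: 42/58/80% within stratum and 71/87/98% pooled. With a one-sided 5% test as well, 100 and 200 per arm give 55/70/88% and 81/92/99%, which are not below the stated values. This stands as a reason to report a range. It does not rescue the paragraph: 55/70/88% does not match the printed 52/67/85%, and the text itself gives 150 and 300.
- **The sample size is not settled within the paragraph.** It also has 850 couples randomized. At 544 completers, two-sided power is close to that stated on the centred reading, and above it (54/72/91% and 83/95/99.7%) if 25% is the higher rate. This stands too. The target of 400 is the figure that the abstract, the Design section and the Sample Size section share, but the 850 chain has to be reconciled with it.
- **The calculation is offered as an example for one of several outcomes.** That is so, but no other power calculation is given.
- **A condensed article may leave detail out.** That does not apply here, since both conflicting numbers are printed in one paragraph.

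**Conclusion.** The error holds. The power statement belongs to 600 analysed couples and the plan has 400. On the only reading found to reproduce the printed figures (two-sided 5%, arms centred on 25%), the planned size delivers 37/50/69% within stratum and 64/79/94% pooled. The detectable differences at 80% power are about 17 and 12 points, against 14 and 10 at the sizes used. Across the two-sided readings, power for 10/12/15 points ranges from 34/45/62% to 42/58/80% within stratum and from 59/74/90% to 71/87/98% pooled. These figures assume that 400 is the number analysed.

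Three stronger readings might be inferred and are not supported:

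- *Every stated power is too high whatever is assumed.* This is shown for a two-sided test at 100 and 200 per arm. The document fixes neither the sidedness nor, because of the 850 chain, a single analysed number.
- *The pooled comparison should become the main one.* The Sample Size section makes pooling conditional on the size and direction of the effects, so that is a design choice and does not follow from the arithmetic.
- *The trial's aim depends on the within-stratum tests.* The Introduction's aim compares effects between couple types, and the Linkage to Care analysis section addresses effect modification with an intervention-by-concordancy interaction test.

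**What to change.** 1. Reconcile the numbers in the Sample Size paragraph: the 400 target, the 850 randomized, the 544 or 510 that the stated attrition leaves, and the 150 and 300 in the power statement. Say whether 400 is the number enrolled or the number analysed.
2. Restate power and the 80%-power detectable differences at the reconciled size. If 400 analysed couples stands, that means 100 per arm within stratum and 200 pooled. On the centred two-sided reading the entries are 37/50/69%, 64/79/94%, 17 points and 12 points.
3. State whether the 5% test is one- or two-sided, and whether 25% is the control rate, the intervention rate or the average of the two. The sponsor should declare what was assumed and adjust the figures in item 2 if it differs from the centred reading.

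If 600 analysed couples were really intended, the 400 in the abstract, Design and Sample Size sections is what needs correcting. If 400 stands, the change is a rewording with no extra couples, and the cost is a less favourable stated power.

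### The confidence-interval restatement of power is incorrect: the stated powers are the chance of excluding zero, not of a lower bound clearing 3, 5 or 8 points

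*Protocol article*

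**What the plan says.** All the relevant text is in the Sample Size section of the protocol article.

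- Assumed rate of change: "we will assume that about 25% of male couples change agreement status after couples counseling".
- Test to be used: "we will use a two-sample test of binomial proportions with type I error rate at 5" percent.
- Test power by serostatus group: "52%, 67%, and 85% statistical power is necessary to detect a difference of 10%, 12%, and 15%, respectively". The comparison these figures refer to is described as "within seroconcordant or serodiscordant groups (ie, comparing 150 male couples per arm". The text words these powers as needed; I read them as the powers available. For the pooled sample (300 per arm) it gives 81/92/99% for the same differences.
- First restatement, which opens: "In other words, under the same conditions, the probability is .52, .67, and .85". The event given those probabilities is worded as follows: "the lower bound of the confidence interval for the proportion change in agreement status in the intervention arm is at least 3" percent different from the control proportion, with 5 and 8 percent for the second and third. It is conditional on the alternative being true.
- Pooled restatement: "at least 80% statistical power will be necessary to detect as little as a 5% difference between the lower bound of the confidence interval". The bound is again that of the intervention arm, set against the control arm.
- The next sentence sets the relevance threshold: "any difference exceeding 5% would be scientifically meaningful and would have public health impact".

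**The concern.** The restatement moves a probability from one event to another. A two-sided 5% test rejects, to a close approximation, when the 95% interval for the difference excludes zero, so power is the probability of that event. A lower bound at or above 3, 5 or 8 points is a stricter event and must be less likely than the lower bound merely exceeding zero.

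The pooled sentence pairs 80% with 5 points immediately before 5 points is named as the smallest difference of interest. A reader could take from this that the trial is adequately powered at its own threshold, and could then read a non-significant result as evidence against a meaningful effect.

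**Working it through.** **Inputs (Sample Size section).** Type I error 5%; 25% changing agreement status; differences d of 10, 12 and 15 points; n = 150 per arm within a serostatus group and 300 pooled; bounds L of 3, 5 and 8 points (150 per arm) and 5 points (300 per arm). Assumed because not stated: a two-sided test, 95% intervals, and arms at 25% ± d/2. This centring reproduces the stated powers.

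**Step 1. Reproduce the test powers.** With p1 = 0.25 − d/2 and p2 = 0.25 + d/2:

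power = Φ[(d − 1.96·SE0)/SE1], where SE0 = √(2·0.25·0.75/n) and SE1 = √{[p1(1−p1) + p2(1−p2)]/n}.

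For n = 150, d = 0.10: SE0 = 0.0500, SE1 = √(0.37/150) = 0.0497, so power = Φ[(0.100 − 0.098)/0.0497] = Φ(0.04) = 0.516.

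| n per arm | 10 points | 12 points | 15 points | Stated |
|---|---|---|---|---|
| 150 | 51.6% | 67.2% | 85.5% | 52/67/85% |
| 300 | 80.9% | 92.6% | 99.0% | 81/92/99% |

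All six agree.

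**Step 2. Which event do these powers describe?** P(lower bound of the difference > 0) = Φ(d/SE1 − 1.96). At n = 150 this is 0.52, 0.68 and 0.86; at n = 300 and d = 0.10 it is 0.81. The stated powers therefore describe excluding zero.

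**Step 3. Probability of the event the text names.** The words describe the intervention arm's own interval compared with the control proportion. With s = √[p2(1−p2)/n]:

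P = Φ[(d − L)/s − 1.96].

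For n = 150, d = 0.10, L = 0.03: s = √(0.21/150) = 0.0374, so P = Φ(1.87 − 1.96) = Φ(−0.09) = 0.46.

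For the interval of the difference, replace s by SE1: Φ(0.07/0.0497 − 1.96) = Φ(−0.55) = 0.29.

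| n, d, L | Stated | One-arm interval | Interval of the difference |
|---|---|---|---|
| 150, 10, 3 | .52 | 0.46 | 0.29 |
| 150, 12, 5 | .67 | 0.46 | 0.29 |
| 150, 15, 8 | .85 | 0.45 | 0.30 |
| 300, 10, 5 | at least .80 | 0.47 | 0.30 |

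Moving the 25% to the control arm or to the intervention arm widens the one-arm results to 0.42-0.51 at 150 per arm and 0.44-0.52 at 300. The results for the difference widen to 0.26-0.37 and 0.27-0.34.

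The pooled sentence does not name its true difference. I take 10 points, the one whose power is 81%. With 12 points and centred arms, the chance of reaching 5 points is 0.75 (one-arm) or 0.52 (difference), still below 0.80. For the interval of the difference, 0.80 needs a true difference of about 14.8 points.

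**Step 4. Likely origin of the thresholds.** The one-arm half-width at 25% is 1.96·√(0.25·0.75/150) = 6.9 points, and 4.9 points at n = 300. Then 10 − 6.9 = 3.1, 12 − 6.9 = 5.1, 15 − 6.9 = 8.1, and pooled 10 − 4.9 = 5.1. These round to 3, 5, 8 and 5. The thresholds thus appear to be expected one-arm lower limits, and an expected limit is reached about half the time. This would also explain why the probabilities in Step 3 hardly change from row to row while the stated ones rise from .52 to .85.

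**Step 5. Power at the relevance threshold.** For d = 0.05 and n = 300: SE0 = 0.0354, SE1 = √(0.37375/300) = 0.0353, so power = Φ[(0.050 − 0.0693)/0.0353] = Φ(−0.55) = 0.29 (0.28-0.31 by placement of the 25%). The true difference with 80% power at 300 per arm is about 9.9 points. Reaching 80% for 5 points would take about 1,177 couples per arm (1,094-1,251 by placement).

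**The case against.** Several points on the other side stand.

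- **The plan never says that it has 80% power for a true 5-point difference.** A reader might infer it from the pooled sentence and the threshold that follows, but the words concern a lower bound, apparently under a true 10-point difference. The 29% answers that inference; it does not refute a stated claim.
- **The sentence names a one-arm interval.** The figure to set against .52/.67/.85 is therefore first 0.42-0.51, and only second 0.29-0.30. On the one-arm reading .52 is nearly right; .67 and .85 are not.
- **The origin of 3/5/8 is inferred.** Centred arms give expected one-arm limits of 2.7, 4.6 and 7.5 points above control, and an intervention arm at 25% gives 3.1, 5.1 and 8.1. Both sets round to 3, 5 and 8, so the text does not settle which was used.
- **Nothing downstream depends on it.** The calculation is offered as an example, and no sample size, analysis or decision rule in the article uses the restatement. The article gives no rule for reading a null result, so misreading is a risk and not a stated intention.

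What does not stand is a defence that an article condenses a fuller document. These are explicit numerical statements, and they fail under each interval and each placement of the 25% tried.

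**Conclusion.** The restatement is wrong as written; the test powers are right for their stated n. A reader might conclude that 52/67/85% and 81/92/99% are miscalculated, but all six reproduce. The error lies only in attaching them to a lower bound above zero. The true probabilities are about 0.42-0.51 (one-arm) or 0.29-0.30 (difference, arms centred on 25%) at 150 per arm, and 0.44-0.52 or about 0.30 for the pooled 5-point claim. If the threshold is read as a true difference, power there is about 29% at 300 per arm.

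This rests on a two-sided 5% test, 95% intervals, the couple as the unit, and a true difference of 10 points behind the pooled sentence. The first is supported by the match to the stated powers; the rest are the ordinary reading.

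**What to change.** Delete the sentence that begins "In other words, under the same conditions, the probability is .52, .67, and .85" and the one containing "at least 80% statistical power will be necessary to detect as little as a 5% difference between the lower bound of the confidence interval". In their place say that:

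- power is the probability that the 95% confidence interval for the arm difference excludes zero;
- at 300 couples per arm, 80% power applies to a true difference of about 10 points, and power for a true difference of 5 points is about 29%;
- a non-significant result does not exclude a 5-point effect.

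Use one set of sample sizes throughout the paragraph. The section also gives a target of 100 couples per arm in each serostatus group (200 per arm pooled), which conflicts with 150 and 300. That is a separate matter to settle; if it is settled at 200 per arm, the figures become about 12 points and 21%, and the test powers quoted for 150 and 300 must be recalculated with it.

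The cost is two sentences and a less favourable statement of what the trial can show. Design and conduct do not change, so the correction can be made while recruitment continues.
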